## Abstract

**Background:**

Traditionally, patients at low risk and high risk of developing dental disease have been encouraged to attend dental recall appointments at regular intervals of six months between appointments. The lack of evidence for the effect that different recall intervals between dental check-ups have on patient outcomes, provider workload and healthcare costs is causing considerable uncertainty for the profession and patients, despite the publication of the NICE Guideline on dental recall. The need for primary research has been highlighted in the Health Technology Assessment Group’s systematic review of routine dental check-ups, which found little evidence to support or refute the practice of encouraging 6-monthly dental check-ups in adults. The more recent Cochrane review on recall interval concluded there was insufficient evidence to draw any conclusions regarding the potential beneficial or harmful effects of altering the recall interval between dental check-ups. There is therefore an urgent need to assess the relative effectiveness and cost-benefit of different dental recall intervals in a robust, sufficiently powered randomised control trial (RCT) in primary dental care.

**Methods:**

This is a four year multi-centre, parallel-group, randomised controlled trial with blinded outcome assessment based in dental primary care in the UK. Practitioners will recruit 2372 dentate adult patients. Patient participants will be randomised to one of three groups: fixed-period six month recall, risk-based recall, or fixed-period twenty-four month recall. Outcome data will be assessed through clinical examination, patient questionnaires and NHS databases. The primary outcomes measure gingival inflammation/bleeding on probing and oral health-related quality of life.

**Discussion:**

INTERVAL will provide evidence for the most clinically-effective and cost-beneficial recall interval for maintaining optimum oral health in dentate adults attending general dental practice.

**Trial registration:**

ISRCTN95933794 (Date assigned 20/08/2008).

## Background

Traditionally, patients at low risk and high risk of developing dental disease have been encouraged to attend dental recall appointments at regular intervals of six months between appointments, with the logic of prevention and early detection of disease [1]. The lack of evidence for the effect that different recall intervals between dental check-ups have on patient outcomes, provider workload and healthcare costs is causing considerable uncertainty for the profession and patients, particularly following the General Dental Council guidance for team working responsibilities around recall intervals [2] and despite the publication of the NICE Guideline [3]. The need for primary research has been highlighted in the Health Technology Assessment Group’s systematic review of routine dental check-ups [4], which found little evidence to support or refute the practice of encouraging 6-monthly dental check-ups in adults. The more recent Cochrane review on recall interval found only one trial, which was assessed as having a high risk of bias, with 185 participants and concluded there was insufficient evidence to draw any conclusions regarding the potential beneficial or harmful effects of altering the recall interval between dental check-ups [5]. The limited evidence from recent observational studies also supports the need for research. Evaluation of the Canadian Non-Insured Health Benefits (NIHB) program found clients with more ‘regular’ check-ups received a standard pattern of service but incurred greater expenditure than those with longer gaps between recalls [6]. Recent evidence from the Dutch health system suggests an increase in General Dentists applying an individualised recall interval from 49% in 2000 to 61% in 2005 and that these dentists provide more frequent periodontal screening than those using a fixed recall interval [7].

Many Clinical Commissioning Groups (CCGs) in England are now seeking to secure adherence to the NICE recall interval guideline as part of their clinical governance responsibilities when commissioning dental primary care services. However, the lack of direct evidence behind differing recall strategies complicates the adoption process, while uncertainty remains within CCGs and among dentists as to how best to implement the guidance in practice.

There is therefore an urgent need to assess the relative effectiveness and value for money of different dental recall intervals in a robust, sufficiently powered randomised control trial (RCT) in primary dental care.

### Trial aim

The aim of this study is to compare the effectiveness and cost-benefit of dental check-ups at different recall intervals (fixed-period six month recall, risk-based recall or fixed-period 24 m recall) for maintaining optimum oral health in dentate adults attending general dental practice.

### Objectives

The primary objectives are to compare (1) gingival inflammation and (2) oral health-related quality of life (OHRQoL) of dentate adults receiving a dental check-up at different recall intervals over a four year period:Fixed-period six month recallRisk-based recallFixed-period 24 m recall

The secondary objectives are to compare the effect of the three recall strategies on periodontal probing depths, dental caries, calculus, preventive and interventive dental treatment, patient anxiety, patient satisfaction with care, oral health knowledge, attitudes and behaviours. The cost-effectiveness and cost-benefit of the three recall strategies will also be assessed as part of the economic evaluation.

## Methods

This is a UK multi-centre, parallel-group, randomised controlled trial with blinded outcome assessment. The trial is set in Primary Dental Care, reflecting the setting within which the vast majority of dentistry is delivered in the UK.

### Trial interventions

The trial interventions are three recall intervals – a fixed-period extended 24 m recall interval, a Risk-Variable-Adjusted-Length recall interval (Risk-based recall) based on the NICE Guideline and a fixed-period conventional six month recall interval.

#### Fixed-period recall intervals

Patient participants allocated to the conventional six month recall interval and extended 24 m recall interval groups will attend their dentist at the scheduled time intervals for a ‘routine’ dental check-up. The content of this check-up will remain as per current practice. A recognised definition of a ‘traditional’ NHS dental check-up is clinical examination, advice, charting including monitoring of periodontal status and report [4]. For participants allocated to the fixed-period recall groups dentists will provide routine care using their current system for examination, record keeping and providing advice.

#### Risk-based recall

Participants allocated to the risk-based recall interval group will attend their dentist at time intervals determined by the evidence-based process outlined in the “2004 NICE guideline on Dental Recall” [2]. The essential steps of the procedure and the risk factors collected at recall examinations are outlined (from the Guideline) in the two figures below (Fig. 1).

**Fig. 1 Fig1:**
[figure not shown]
The process of recall interval selection

The recommended stages in establishing the appropriate recall interval are:**Establishing the Age Range** – establishing the individual patient’s age. In the case of this trial all patients will be adults of 18 years of age or more.**Consideration of Risk Variables** – identification of the pertinent risk and protective factors present for each patient from the checklist and the Comprehensive Oral Health Examination, leading to the evaluation of the impact of these factors in the context of the patient’s past levels of oral health and current disease experience and then, consideration of a likely range of recall intervals.**Integration and Prediction of Recall Need** - use of all of the information obtained by the dental team in order to predict the potential level of threat to maintaining oral health and controlling disease for this patient and, from this, to judge the most appropriate next recall interval.**Discussion** – to explicitly discuss the recommended recall interval with the patient, explain the influencing factors in setting the recall and record the agreed interval (or any reason given by a patient in disagreement).**Review** - at each check-up review (oral health review), the appropriateness of the just-concluded interval is reviewed by dentist and patient and the recall interval is reset according to the experience from the last period along with any change in the risk and protective variables identified at re-examination.

The frequency of recall interval appropriate for an individual patient will depend on the likelihood that specific diseases or conditions may develop or may progress beyond the control of secondary prevention. The guidance (built on extensive consensus methods and the limited evidence available) indicated that the recall interval range should vary from three to 24 m, according to risk. Training in assessment of relevant risk and protective factors to consider when allocating a recall interval will be provided by means of a specifically developed online training package based on the relevant NICE Guideline. Online training in allocation of risk-based recall will be carried out annually.

It is anticipated that by carrying out a comprehensive history and oral examination the dentist will be better informed to provide an accurate risk assessment and more appropriate preventive and interventive treatment recommendations leading to improvements in maintaining oral health, in oral health related quality of life and will result in less dental anxiety for the patient.

#### Recall strategy allocation

Prior to randomisation, all patient participants will be clinically examined by their dentist to determine suitability for randomisation to the 24 m recall arm. A detailed risk assessment is not part of this suitability examination and the decision made will be based on current practice, with routine examination criteria and record keeping.

Randomisation will be organised within two strata depending on the recruited participant’s suitability to enter the 24 m arm:

1) Twenty-four month recall versus risk-based recall versus six month recall;

2) Risk-based recall versus six month recall.

Randomisation to trial arms will be carried out using the automated central randomisation service at the Centre for Healthcare Randomised Trials (CHaRT) at the University of Aberdeen, with 24 h access by telephone. Allocation will take place after the suitability examination. Eligible participants will be randomised in equal proportions within each of the two strata according to a minimisation algorithm including dentist, age, filled teeth - FT (FT ≤ 8 or FT > 8 [8]) and absence of gingival bleeding on probing. There will be separate, identical algorithms for the two strata. The design is summarised in the graphic below (Fig. 2).

**Fig. 2 Fig2:**
[figure not shown]
Study design

### Study recruitment and allocation

#### Identifying and recruiting dentists

We are aiming to recruit 50 general dental practitioners from across the UK, including dentists in England, Scotland, Wales and Northern Ireland, representing a cross-section of practitioners in terms of urban/rural area, community-level socio-demographics, and fluoridated or non-fluoridated communities. It is a requirement that all recruited dentists provide some NHS dental services for adults.

Dentists will be recruited to the trial through local research networks, advertising in the dental press, and trial team attendance at research network meetings. The Trial Office in Dundee (TOD) will send potential dentist participants an invitation letter, describing the study and interested dentists invited to a local information and recruitment session.

#### Identifying and recruiting patients

Recruitment of patient participants will be achieved through standard procedures and agreements for primary care research in the four nations. In Scotland co-ordinators from the Scottish Primary Care Research Network (SPCRN) will assist practice staff managing previously scheduled appointments, by including Patient Information Leaflets and an invitation to participate, in the appointment letters. In England, Wales and Northern Ireland appropriate regional Comprehensive Local Research Networks (CLRNs) will provide the identical service. The TOD will not have access to any data prior to the participant consenting to take part in the trial. At this stage, those who clearly express no interest in taking part will be sent an alternative check-up appointment to see their dentist. More than one dentist per practice can recruit participants into the trial. At the recruitment appointment the dentist will discuss the trial with the potential participants and answer any questions. Those who state they do not wish to take part will then receive their check-up as normal. Eligibility of those who express an interest in taking part will be confirmed against the trial inclusion and exclusion criteria. Those who are eligible will be consented to the trial by their dentist. The dentist will then examine the patient participant for suitability for randomisation to the 24 m arm.

### Inclusion criteria

Adult patients (≥ 18 years of age) who:Are dentateHave visited their dentist in the previous two yearsReceive their dental care as an NHS patient

### Exclusion criteria

Patients who have a medical condition indicating increased risk of bleedingImmuno-compromised patients

### Outcome measures

#### Primary outcomes

##### Clinical

Gingival inflammation/bleeding on probing at the gingival margin

##### Patient centred

Oral health-related quality of life (OHRQoL)

#### Secondary outcomes

##### Clinical

Dental cariesPeriodontal pocket depthCalculusPreventive and interventive care

##### Patient centred

Dental anxietyOral health related knowledge, attitudes, and behavioursUse of and reason for use of dental servicesSatisfaction with care

##### Service-providers

Dentist attitude towards dental recall strategies

#### Economic outcomes

NHS costsPatient incurred costsGeneral population preferences, willingness to payNet benefits (Benefits – costs)Generic Quality of Life, measured using the EQ-5D-3 LQuality adjusted life years (QALYs)Incremental cost per QALY gained

There are two primary outcomes: the primary clinical outcome is periodontal disease as measured by gingival bleeding, and the primary patient centred outcome is oral health-related quality of life as measured by the Oral Health Impact Profile-14 (OHIP-14). These are the outcomes that the study is powered at 80% to detect meaningful changes. Other measures are collected as secondary outcomes. Given the complex intervention and the unknown correlation between the two different dimensions of the study (patient and clinical), the study will not correct the *p*-value for multiplicity of tests.

### Data collection and processing

Participating dental practices will be expected to maintain a file of essential trial documentation which will be provided by the TOD. This will include documenting participant recall appointment attendance, dental treatment required, and duration of recall appointments.

### Collection of clinical outcome measures

Clinical outcomes will be measured at four years follow-up by trained outcome assessors who are blinded to allocation. Clinical outcome measures will be collected within four months either side of the four year anniversary of participant randomisation. Gingival inflammation as bleeding will be measured according to the Gingival Index of Loe [9] by running a UNC periodontal probe circumferentially around each tooth just within the gingival sulcus or pocket. After 30 s, bleeding will be recorded as being present or absent on the buccal and lingual surfaces. The colour-coded UNC periodontal probe will be used to measure periodontal pocket depth and then the presence of calculus. Clinical outcomes will be measured for all included teeth at six sites per tooth [mesiobuccal, midbuccal, distobuccal, mesiolingual, midlingual, and distolingual]. Third molar teeth will be excluded from clinical examination, except where a second molar tooth is absent and the third molar tooth has drifted mesially to occupy the position of the second molar. The sequence of scoring will be gingival inflammation, followed by periodontal pocket depths and calculus. The periodontal examination will take place first, then teeth brushed by the examiner and caries examination carried out.

Measurements of caries experience at the enamel and dentine threshold will be made using the validated International Caries Detection and Assessment System (ICDAS) [10–12] in the examination of clean and dry teeth aided by a ball-ended explorer that is used to remove any remaining plaque and debris and to check for surface contour, minor cavitation or sealants. Third molar teeth will be excluded from clinical examination, except where a second molar tooth is absent and the third molar tooth has drifted mesially to occupy the position of the second molar. All surfaces of all teeth excluding third molars will be examined and the caries status recorded.

Throughout the four year trial follow-up period recruited dentists will complete specially developed forms for each participant, documenting dental treatment provided during the trial period, including scheduled and re-scheduled check-up appointments. Details of preventive and interventive treatment provided during the trial period will also be accessed through the routinely collected data in all participating regions in the UK.

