### Collection of economic measures

The costs of all dental treatment provided by NHS dentists to patients, including the costs of planned check-ups are captured through the routinely collected data held by Information Services Division (ISD) in Scotland, NHS Information Centre, business services authority (BSA) in England and Health and Social Care Business Services Organisation (HSCBSO) in Northern Ireland. Time, travel and treatment costs associated with visits to the dentist will be collected through baseline questionnaires administered to trial participants on entry to the trial. Private dental care and use of other NHS services for dental issues are also collected by patient questionnaire.

Benefits to patients of the three intervention arms will be measured in two ways. Public preferences will be elicited regarding the value they place on different recall strategies using a discrete choice experiment (DCE) (see economic analysis). The DCE will be administered to a separate sample of the public obtained from electoral rolls over the course of the trial. Benefits are also measured in terms of QALYs (see above).

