#### Estimation of cost-effectiveness

The economic analysis will assess whether fixed-period 24-month or risk-variable-adjusted length dental recall represents an efficient use of NHS resources compared to the traditional fixed-period six-month recall. Cost-effectiveness will be measured in terms of the incremental cost per QALY gained and in terms of net benefits (cost-utility analysis and cost-benefit analysis).

The incremental cost per QALY is estimated by dividing the difference in mean total costs by the difference in QALYs between the arms of the Trial. This ratio can be compared to the conventional threshold of £30,000 per QALY. Bootstrapping is used to generate Cost-Effectiveness Acceptability Curves (CEAC). The CEAC shows the probability that the different recall strategies are cost-effective compared to usual care at various thresholds of cost-effectiveness. The threshold represents the decision-maker’s willingness to pay for an additional QALY. The CEAC represents the joint uncertainty surrounding the cost and QALY pairs.

The WTP values are mapped to recall strategy and trial outcomes and are directly compared with the costs to produce net benefits for each recall strategy. The recall strategy with the highest incremental net benefit compared to six-monthly recall is the most efficient option. A net benefit curve is produced which shows the probability of the net benefits being larger than different potential thresholds.

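### Treatment and costs are counted over four years, and the last planned check-up falls due on the closing month: up to 24 months of need may be left out in the 24-month arm, against up to 6 in the six-month arm

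*Protocol article*

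**What the plan says.** The abstract's Methods paragraph sets the length of the study: "This is a four year multi-centre, parallel-group, randomised controlled trial with blinded outcome assessment". Two of the interventions are "a fixed-period extended 24 m recall interval" and "a fixed-period conventional six month recall interval" (*Trial interventions*).

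Preventive and interventive care is a secondary clinical outcome. Under *Collection of clinical outcome measures* it has two sources. For the dentists' forms: "Throughout the four year trial follow-up period recruited dentists will complete specially developed forms for each participant, documenting dental treatment provided during the trial period". For the NHS databases: "Details of preventive and interventive treatment provided during the trial period will also be accessed through the routinely collected data". Both are limited to treatment provided within the trial period. The same section allows clinical outcomes to be measured within 4 months of the fourth anniversary, but states that allowance for clinical outcomes only.

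*Collection of economic measures* says: "The costs of all dental treatment provided by NHS dentists to patients, including the costs of planned check-ups are captured through the routinely collected data". It gives no end date of its own. *Estimation of cost-effectiveness* then uses these costs: "The incremental cost per QALY is estimated by dividing the difference in mean total costs by the difference in QALYs between the arms of the" [study]. It describes no extrapolation. *Sensitivity analysis* lists the discount rate, unit costs, missing data and centre variation, but not the point at which counting stops.

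**The concern.** Treatment is recorded only when a visit leads to it. The randomised factor is the spacing of those visits, so closing every arm's count in the same calendar month need not treat the arms alike. A cut-off that falls on a planned visit puts at risk the need built up since the previous visit, and that backlog is four times as long in the 24-month arm as in the six-month arm.

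The preventive and interventive care outcome and the NHS and patient costs are at stake. The costs feed both the cost per QALY and the net benefit, and cost-benefit is part of the stated trial aim. Treatment pushed past the cut-off would appear as a saving for the longer interval when it is only a deferral.

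**Working it through.** The article gives no figure for this point, so there is none to reproduce. The check is arithmetic on the recall schedule.

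**Inputs from the article.** Follow-up is 48 months. The fixed recall intervals are 6 and 24 months.

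**Step 1: planned check-ups.**
- Six-month arm: months 6, 12, 18, 24, 30, 36, 42 and 48, so 8 visits.
- 24-month arm: months 24 and 48, so 2 visits.

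The last visit in each arm falls due exactly at the cut-off.

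**Step 2: need left uncounted** = 48 − month of the last counted check-up.

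| Month-48 visit and its treatment | Six-month arm | 24-month arm |
|---|---|---|
| Counted | 48 − 48 = 0 months (8 of 8 visits) | 48 − 48 = 0 months (2 of 2 visits) |
| Not counted | 48 − 42 = 6 months (1/8 = 12.5% of visits lost) | 48 − 24 = 24 months (1/2 = 50% of visits lost) |

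**Step 3: effect on recorded treatment at the bound.** Assume that need accrues evenly and equally in both arms, that no prior need is carried in, and that the month-48 course is not counted. Let u be the share of need met at unscheduled visits (an assumption, varied below). The recorded share is u + (1 − u) × (month of last counted check-up)/48.

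| u | 24-month arm | Six-month arm | Ratio |
|---|---|---|---|
| 0 | 24/48 = 0.500 | 42/48 = 0.875 | 0.57 |
| 0.25 | 0.25 + 0.75 × 0.500 = 0.625 | 0.25 + 0.75 × 0.875 = 0.906 | 0.69 |
| 0.5 | 0.5 + 0.5 × 0.500 = 0.750 | 0.5 + 0.5 × 0.875 = 0.9375 | 0.80 |

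**Step 4: treatment arising from the baseline examination.** Every participant is examined before allocation. If treatment lags the visit, that examination's treatment falls inside follow-up in every arm. With p months of prior need and u = 0, the ratio is (24 + p)/(42 + p). For p = 6 it is 30/48 = 0.63, and for p = 24 it is 48/66 = 0.73. Both p values are assumptions; 24 corresponds to the inclusion limit of a dental visit in the previous two years. The ratio moves towards 1, but the absolute gap of 18 months of need (42 − 24) does not change.

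**Step 5: between zero and the bound.** Appointment timing was simulated with an assumed SD of 1 month, a mean shift of −1 to +2 months, and 0 or 1 month from visit to treatment, on fixed and on drifting schedules. The mean uncounted gap was 2.2 to 5.4 months in the six-month arm and 3.9 to 22.6 months in the 24-month arm. It was larger in the 24-month arm in all 20 scenarios. These inputs are assumptions, not figures from the article.

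**The case against.** The strongest reply is that nothing in the article excludes the month-48 check-up. Since 48 is a multiple of both intervals, counting that visit and its treatment leaves no gap in either fixed arm, and an extraction date could reasonably sit in a fuller plan. This stands as to size: the bias may be zero. It does not remove the point, because the article does state a window, treatment provided within the trial period, and half of one arm's planned visits sit on its edge against one eighth of the other's.

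Further points stand in part:

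- *Data collection and processing* has practices record treatment required as well as attendance, so need found at an on-time month-48 visit may be on file. That does not help when the visit is late, and the outcome and costs rest on treatment provided.
- Participants may seek care between recalls (*Ethical considerations*), and treatment from the baseline examination may fall inside follow-up. Both make 0.57 an extreme.
- Disease present at four years is measured by blinded examination in every arm, and willingness-to-pay values are mapped to trial outcomes. A reader would therefore see any extra disease, but its treatment would still be missing from the treatment count and the costs.
- Costs incurred within four years are correct as spending, and QALYs cover the same period. The economic question, however, is whether a recall strategy is good value for the NHS, and a bill that falls just after the cut-off belongs to that strategy.
- The ratios describe treatment need, not money. The Discussion notes that some practices are paid in bands, so cost need not follow accrued months. No effect on cost or on cost per QALY has been computed.

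**Conclusion.** The point holds as a conditional one. The counting window can omit up to 24 months of need in the 24-month arm against up to 6 in the six-month arm. Where it does, the error favours 24-month recall in the treatment and cost comparisons. The size runs from zero to that bound. At the bound, with even accrual and no prior need, the recorded-treatment ratio with no true difference would be about 0.57 with no unscheduled care and 0.80 if half of need is met at unscheduled visits, and nearer to 1 once treatment from the baseline examination is included.

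A reader might infer that need in months 24 to 48 certainly goes uncounted, or that recorded treatment will be 43% lower in the 24-month arm. The article does not support either: it leaves the handling of the month-48 visit open, and the cost cut-off is implied by the trial period, not written. Nor does the point reach the primary outcomes. Bleeding and OHIP-14 do not depend on the treatment and cost counts.

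**What to change.** State that in every arm the treatment and cost counts include the check-up due at month 48 and the course of treatment opened at it. Give all arms the same lateness allowance, for example the 4 months already used for clinical outcomes. Extract routine data late enough to capture that course, but exclude any later recall check-up. Simply moving the cut-off to month 54 would bring in another six-month check-up and recreate the same edge.

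As a separate sensitivity analysis, close the count at month 48 and add in every arm the unit cost of treating unrestored dentine-threshold lesions found at the blinded four-year ICDAS examination. This also covers risk-based participants caught between recalls. It must not be added on top of the extended count, or the same lesion could be costed twice.

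The cost is a few months' wait for the economic data, a sentence or two in the plan and one extra analysis. No extra visits are needed.
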